### Logistical issues

Given the multi-institutional nature of this clinical trial, several pre-requisites exist for centres to participate in this clinical trial. Centres must have Helical Tomotherapy technology available at their centre in order to participate in this clinical trial. A copy of local REB and local clinical trial unit approval letters must be sent to coordinating centre PI prior to initiation of this study. Participating centres must submit a three metastases test case planned with HT with phantom delivery and measurement data to demonstrate the centre's ability to deliver protocol treatment. This three-metastasis test case will be provided to the participating sites by the London investigators in order to provide a relative quality assurance assessment of the various participating centres. This planning and phantom data will require quality assurance approval by physics PI prior to clinical trial initiation and patient enrolment. In conjunction with this physics submission, all default planning importance, penalty factors, and precedence factors to be submitted to and approved by coordinating centre PI. Any required modifications to the protocol, letter of information, consent form, and/or local case report forms need to be approved by coordinating centre prior to patient enrolment to ensure compatibility with the central study database.

### Study procedures

All patients must have a contrast enhanced MRI brain within six weeks of study enrolment, a dictated history including steroid and anti-convulsant usage, dictated physical examination, screening neurological examination with mini-mental status examination (MMSE), FACT-Br HRQoL questionnaire completed during enrolment visit, and a baseline NCI-CTC V3 toxicity assessment. All medications received by the study subjects prior to initiation will be recorded on the subject's case report form. Specific treatment simulation and planning details with relation to the delivery of 60 Gy SIB with 30 Gy WBRT are available in the attached clinical protocol (see Additional file 1). Steroid, anticonvulsant use and cancer therapies/medications delivered after treatment initiation will be recorded. Cytotoxic chemotherapy is not permitted during the radiotherapy. Patients may be treated with glucocorticoids and prophylactic anticonvulsants as required.

Follow-up visits and assessments (KPS, NCI CTC V3 Toxicity, FACT-Br HRQoL, steroid, and anticonvulsant medications) will occur at the following intervals post treatment: 6 weeks and 3, 6, 9, 12, 18, and 24 months. Contrast enhanced MRI brain scans will occur at 3 and 6 months after radiation therapy completion. Other CT or MRI based imaging will occur thereafter according to institutional standard of care guidelines prior to subsequent visits. Participating centers will be required to declare their standard of care imaging past 6 months to the study principal investigator prior to patient enrolment.

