## Methods/Design

### Study objectives/hypotheses

The primary objective of interest in this study is to obtain an estimate of median overall survival (OS), six-month intracranial control (ICC) and six-month intralesional control (ILC), in order to ensure that the fractionated treatment is not substantially inferior to RTOG historical controls. Secondary objectives include longitudinal RECIST criteria response rates, cognitive assessment, health-related quality-of-life, and treatment-related toxicity.

The study null hypothesis is that fractionated HT SIB RT is not inferior to reported RTOG 9508 SRS outcomes of OS, ICC, and ILC. The study alternative hypothesis is that fractionated HT SIB RT is inferior to ANY reported historical RTOG SRS outcomes of OS, ICC, and ILC.

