### Study design overview

The proposed clinical trial is designed to be a phase II multi-institutional assessment of helical tomotherapy simultaneous in-field boost radiation to 1-3 brain metastases in patients with a variety of primary malignancies. A common dose of the 60 Gy MTD in 10 fractions will be used from the result of the preceding phase I dose-escalation trial as coordinated by the London Regional Cancer Program. No blinding or randomization procedures are required in this protocol. However, maximal accrual to the following four bins will be respected in order to balance overall patient population with respect to the primary site of disease as well as brain metastasis number for an accurate historical comparison to the RTOG stereotactic trial.

Bin #1: Lung Primary and Solitary Metastasis, n = 33

Bin #2: Lung Primary and 2-3 Metastasis, n = 19

Bin #3: Non-Lung Primary and Solitary Metastasis, n = 26

Bin #4: Non-Lung Primary and 2-3 Metastasis, n = 15

Inclusion criteria for this research protocol will include: a histologic diagnosis of primary cancer, a contrast-enhanced MRI demonstrating 1-3 metastases within 6 weeks of study enrollment, patient age ≥ 18 years, KPS ≥ 70, patient to be available for subsequent follow-up appointments and diagnostic testing, anticipated survival (independent of the brain metastases) > 3 months, patient informed consent obtained, and the extracranial disease must be controlled, to be treated, or absent. Exclusion criteria for this protocol will include: metastases not suitable for synchronous boost (> 3 lesions or any lesion size > 3 cm in maximum dimension, metastases close to (within 5 mm) brainstem or optic apparatus, cytologic or imaging evidence of leptomeningeal spread, intracranial extension of an osseous (calvarial) metastasis, or evidence of intraventricular or subependymal growth), no prior histologic confirmation of malignancy, underlying medical condition precluding adequate follow-up, prior cranial radiotherapy, concurrent cytotoxic chemotherapy, lack of informed consent, patient unable to complete study questionnaires, and any contraindications to MRI or gadolinium contrast.

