### Study endpoints and sample size calculation

The primary outcome measure of this study has been selected after review of the literature regarding recent (RTOG 9508 and RTOG 0614) clinical trials assessing radiotherapy for brain metastases. The RTOG trials have focused on overall survival and intracranial control of disease as endpoints of interest. For example, patients treated with WBRT + SRS on the RTOG 9508 trial experienced median overall survival of approximately 6.5 months with 6-month intracranial tumour progression-free rate of approximately 85% and 6-month local (lesion) control rate of approximately 90%.

We hypothesize HT would be considered unsuitable for further study if the median OS for patients treated with the HT SIB technique is degraded by 2 months, or the intracranial progression-free rates (ICC and ILC) are inferior by 10% or greater compared to the expected results with treatment by WBRT + SRS. In other words if in our phase II trial OS ≤ 4.5 months, 6-month intracranial progression-free (ICC) rate is ≤ 75%, OR 6-month local control (ICL) rate is ≤ 80%, HT SIB RT would be considered to be inferior to the RTOG historical control data for WBRT+SRS and should not proceed to phase III testing. To account for multiple testing, each statistical assessment of each individual outcome will be set at the α = 0.025 and β = 0.10 levels. All tests will be 1-sided and calculations will be performed using the on-line calculators available at (http://www.crab.org/Calculators.asp - Southwest Oncology Group (SWOG) Cancer Research and Biostatistics (CRaB) department). It is assumed that for this study, patients will be accrued over two years and there will be 6 months of follow-up after the last patient is accrued. Therefore, for overall survival, set H0: median OS = 6.5 months versus HA: median OS = 4.5 months, 93 total patients are required. For the ICC progression-free rate, set H0: 6-month rate = 85% versus HA: 6-month rate = 75%, 71 total patients are required. For ILC progression-free rate, set H0: 6-month rate = 90% versus HA: 6-month rate = 80%, 53 total patients are required. Given the actuarial nature of the six-month OS endpoint, no additional adjustment for loss to follow-up is required. Thus, we will aim to accrue a total of 93 enrolled and on-treatment patients, as this will be sufficient to assess all outcomes of interest (OS, ICC, ILC).

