### Statistical analysis plan

Descriptive statistics will be used to summarize the patient population, tumor- and treatment-related parameters, treatment toxicities, causes of death, location of intracranial, intralesional and extracranial progression and performance status. Time to event outcomes will be estimated using the Kaplan-Meier method. Tables and plots will be used to better illustrate results. 95% confidence intervals will be constructed for outcomes of interest. A calculation of actuarial six-month OS, ICC, and ILC will be performed after all patients have had 6 months of potential follow-up in order to assess the phase II research question to either accept or reject the study hypothesis that HT SIB RT is a clinically appropriate alternative to WBRT+SRS.

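### Six-month ICC and ILC are read from a Kaplan-Meier curve at the same nominal time as the last scheduled MRI, so progressions first seen on a late 6-month scan (or on nearly every one, if time runs from enrolment) fall after the landmark and the rates read too high

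*Protocol article*

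**What the plan says.** The primary objective (Protocol article, Study objectives/hypotheses) is an "estimate of median overall survival (OS), six-month intracranial control (ICC) and six-month intralesional control (ILC"). The Statistical analysis plan section names the estimator, "Time to event outcomes will be estimated using the Kaplan-Meier method", and the landmark: "A calculation of actuarial six-month OS, ICC, and ILC will be performed after all patients have had 6 months of potential follow-up".

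The Study procedures section times assessments from the end of treatment. Visits "will occur at the following intervals post treatment: 6 weeks and 3, 6, 9, 12, 18, and 24 months", and for imaging "Contrast enhanced MRI brain scans will occur at 3 and 6 months after radiation therapy completion". Later imaging follows each institution's standard of care. These two MRIs are therefore the only protocol scans up to the landmark.

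The sample size section assumes that "patients will be accrued over two years and there will be 6 months of follow-up after the last patient is accrued". The Study timelines section expects accrual to end in June 2013 and six-month follow-up to be complete in January 2014. The article gives no time origin for ICC or ILC and does not say how a progression found on a scheduled scan is dated.

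**The concern.** A Kaplan-Meier curve steps down on the date a progression is recorded. For a progression without symptoms, that is the scan date. A progression arising between the two protocol scans and first seen on the second enters the six-month rate only if the second scan is dated no later than month 6. That scan is nominally at month 6 from radiotherapy completion, so on any earlier origin it falls past the landmark.

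The error runs one way: late detection can only raise measured control. The plan stops HT if the six-month ICC is 75% or lower, or the six-month ILC 80% or lower. The trial exists to catch a treatment that is materially worse, and this error works against catching one.

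**Working it through.** **1. What the follow-up sentence in the sample size section does.** It is an input to the sample size calculation. With accrual A = 24 and follow-up F = 6 months, hazard λ = −ln(S)/6 and event probability p = 1 − [exp(−λF) − exp(−λ(A+F))]/(Aλ), the one-sample exponential formula on the cube-root scale is

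N = [1.960·λ0^(1/3)/√p0 + 1.282·λ1^(1/3)/√p1]² / {9·[λ1^(1/3) − λ0^(1/3)]²}

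- ICC, 85% v 75%: p0 = 0.375, p1 = 0.554, N = 70.5, rounded up to 71 as stated.
- ILC, 90% v 80%: p0 = 0.266, p1 = 0.471, N = 52.9, rounded up to 53 as stated.

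So the sentence fixes study duration. It does not set the clock for ICC or ILC, and both plausible clocks have to be examined.

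**2. Inputs for the size of the bias.**
- From the article: scans at 3 and 6 months after radiotherapy; limits of 75% (ICC) and 80% (ILC); 93 patients; median survival 6.5 months under the null; a 10-fraction course.
- Assumed: constant progression hazard; death as non-informative censoring; five fractions a week, so about 0.5 month from the start to the end of treatment; scan dates scattered evenly by up to 1 or 2 weeks either side of the due date; a share f of progressions (0, 30% or 50%) found clinically when they occur.

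**3. Clock from radiotherapy start or enrolment (scans at about 3.5 and 6.5 months).** The second scan contributes nothing by month 6, so

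apparent rate = S(3.5) − f·[S(3.5) − S(6)], where S(3.5) = S(6)^(3.5/6)

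- ICC truly 75%: S(3.5) = 0.75^(3.5/6) = 84.6%. With f = 50%: 84.6 − 0.5 × 9.6 = 79.8%.
- ILC truly 80%: S(3.5) = 0.80^(3.5/6) = 87.8%. With f = 50%: 87.8 − 0.5 × 7.8 = 83.9%.

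**4. Clock from radiotherapy completion (scans at about 3 and 6 months).** With symmetric scatter, about half of the second scans are late. To a first approximation the apparent rate lies midway between S(3) and S(6).

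- ICC: S(3) = √0.75 = 86.6%; midway (86.6 + 75)/2 = 80.8%. With f = 50%: 75 + 0.5 × 5.8 = 77.9%.
- ILC: S(3) = √0.80 = 89.4%; midway (89.4 + 80)/2 = 84.7%. With f = 50%: 80 + 0.5 × 4.7 = 82.4%.

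**5. Simulation** (93 patients, exponential progression and death, Kaplan-Meier read at 6.0 months). Results agree with steps 3 and 4 to within about a percentage point:

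| Clock | True rate | f = 0 | f = 30% | f = 50% |
|---|---|---|---|---|
| RT completion, ±1 to 2 weeks | ICC 75% | 81% | 79% | 78% |
| Accrual, scans 0.5 month later | ICC 75% | about 84% | 82% | 80% |

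For a true ILC of 80%, the corresponding ranges are 83–85% and 84–88%. Widths of 1 and 2 weeks give nearly the same answer, because what matters is the share of scans that are late, not by how much.

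**6. Check of the remedies.** Assigning scan-detected progressions to month 3 or 6 brings the simulated ICC back to about 75% on both clocks. Reading the curve at 7 months on the accrual clock does not: it captures scans at about 6.5 months, so a true 75% reads 0.75^(6.5/6) = 73.2% and a true 85% reads 83.9%, against six-month benchmarks.

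**The case against.** Three stronger readings are tempting, and the article does not support them.

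- *ICC and ILC are counted from accrual, so the 6-month MRI always misses the landmark.* No section says so. The sentence that "there will be 6 months of follow-up after the last patient is accrued" is a duration assumption (step 1), and Study procedures counts visits and scans from the end of treatment. The larger figures are therefore conditional on an enrolment or treatment-start clock.
- *The data cut precedes the last patients' 6-month MRI.* Study timelines leaves about seven months between the end of accrual and the end of follow-up, which is room for that scan. The written trigger is only ambiguous about what six months is counted from.
- *An inferior treatment will look non-inferior to RTOG 9508.* The 85% and 90% benchmarks may carry a detection delay of their own. The net bias depends on that trial's origin and scan schedule, which are not given.

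It is also fair that the full protocol (Additional file 1, not shown) may define the origin and scan windows, that the windows here are assumed, and that some progressions surface between scans. The phase I results report early intracranial recurrence as the reason two patients had no 3-month imaging; f = 0 is therefore an extreme. Loss of power is not quantified here because the article names no test for the landmark rates.

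The point still goes beyond missing detail. The stated estimator, landmark and scan schedule together give an upward-biased rate under either plausible origin. From radiotherapy completion it disappears only if scans fall on the landmark day and are counted there; even an early scan misses what arises between it and month 6.

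**Conclusion.** The concern holds in conditional form. As written, the six-month ICC and ILC tend to exceed the true rates, by an amount that depends on a time origin the article does not state. For a treatment exactly at the plan's limits, the excess is about 3 to 6 percentage points for ICC and 3 to 5 for ILC if time runs from radiotherapy completion, and about 5 to 9 and 4 to 8 if it runs from accrual or treatment start. In each case examined, the expected reading lies above the limit it should meet. These figures rest on constant hazard, non-informative censoring by death, an assumed scan scatter, a two-week course and 0 to 50% clinical detection. They describe bias against the true rate. Bias against the RTOG 9508 benchmark is undetermined.

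**What to change.** 1. State the time origin for ICC and ILC.
2. Assign a progression found on a protocol MRI to its nominal visit (3 or 6 months), with a stated scan window, so that the six-month rate includes the completed 6-month MRI. Alternatively, use an interval-censored estimator evaluated at six months.
3. Make the analysis trigger the last patient's 6-month post-radiotherapy MRI. The January 2014 date already allows for this.
4. Do not move the reading to 7 months while keeping six-month benchmarks; that tilts the comparison against HT.
5. If the RTOG 9508 origin and scan schedule can be established, state them beside the benchmarks.

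The cost is a few sentences of analysis wording and slightly more analysis work. No patients or scans are added. The reported control rate will be slightly less favourable.

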### Statistical analysis plan

Descriptive statistics will be used to summarize the patient population, tumor- and treatment-related parameters, treatment toxicities, causes of death, location of intracranial, intralesional and extracranial progression and performance status. Time to event outcomes will be estimated using the Kaplan-Meier method. Tables and plots will be used to better illustrate results. 95% confidence intervals will be constructed for outcomes of interest. A calculation of actuarial six-month OS, ICC, and ILC will be performed after all patients have had 6 months of potential follow-up in order to assess the phase II research question to either accept or reject the study hypothesis that HT SIB RT is a clinically appropriate alternative to WBRT+SRS.

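### Overall survival is sized and limited on the median, but the analysis plan decides on six-month survival, for which no hypotheses or limit are given

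*Protocol article*

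**What the plan says.** Under Study objectives/hypotheses, the primary objective is to "obtain an estimate of median overall survival (OS), six-month intracranial control (ICC) and six-month intralesional control (ILC"). The six-month label belongs to the two control rates, and OS is a median.

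Study endpoints and sample size calculation keeps to this. The OS hypotheses and size are "set H0: median OS = 6.5 months versus HA: median OS = 4.5 months, 93 total patients are required", and the technique is judged unsuitable if OS is 4.5 months or less, which can only be a median. Control rates of 75% or less (intracranial) and 80% or less (intralesional) at six months are the matching limits for the other two outcomes. On error rates, "each statistical assessment of each individual outcome will be set at the α = 0.025 and β = 0.10 levels" and "All tests will be 1-sided". On timing, "patients will be accrued over two years and there will be 6 months of follow-up after the last patient is accrued".

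The same section then justifies making no allowance for loss to follow-up with the words "Given the actuarial nature of the six-month OS endpoint".

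The Statistical analysis plan section says: "A calculation of actuarial six-month OS, ICC, and ILC will be performed after all patients have had 6 months of potential follow-up". It gives the purpose as accepting or rejecting the study hypothesis. It also provides for Kaplan-Meier estimates and 95% confidence intervals, but ties no decision to the median.

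**The concern.** Median OS and six-month OS are different decision quantities. A test against a median, of the kind that gives about 93 patients, uses every death up to the analysis date. Six-month OS ignores every death after six months. The text supports both as the basis of the OS decision, and for the six-month version it supplies nothing to test against.

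OS is the outcome that fixes the trial size (93, against 71 and 53 for the control rates), and the result decides whether a phase III trial follows. Inferiority is the alternative hypothesis here, so lost power favours the experimental technique: a treatment as poor as the alternative is more likely to pass.

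**Working it through.** **Inputs, all from the sample-size section.** One-sided alpha 0.025 (z = 1.960); power 90% (z = 1.282); medians 6.5 and 4.5 months; 24 months of accrual, taken as uniform; 6 months of further follow-up. Exponential survival is an assumption, with hazard λ = ln 2 / median.

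**1. Reproducing the 93.** The probability that a patient's death is observed is p = 1 − [exp(−6λ) − exp(−30λ)] / (24λ). This gives p0 = 0.810 and pA = 0.895. On the log-hazard scale:

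n = [(1.960/√0.810 + 1.282/√0.895) / ln(6.5/4.5)]² = [(2.178 + 1.354) / 0.3677]² = 92.3, so 93.

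Other one-sample exponential forms:

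| Form | n |
|---|---|
| Required events (77.7) divided by pA | 87 |
| Hazard scale | 87 |
| Cube-root transform | 90 |
| Log-hazard | 93 |
| Required events divided by p0 | 96 |
| Mean-survival scale | 103 |

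The stated size therefore belongs to this family of all-deaths tests. The exact formula is not established (see the objection).

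**2. Power of the all-deaths test at 93.** (√93 × 0.3677 − 2.178) × √0.895 = 1.295, so power is 90.2%. Simulation of 20,000 trials gives 92%, at a type I error of about 3.0% for the simple log-hazard version. Expected deaths are 93 × 0.810 = 75 under the null and 93 × 0.895 = 83 under the alternative.

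**3. Six-month OS under the same model.** S(6) = 0.5^(6/6.5) = 52.7% under the null and 0.5^(6/4.5) = 39.7% under the alternative. For 90% power:

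n = [(1.960 × √(0.527 × 0.473) + 1.282 × √(0.397 × 0.603)) / 0.1305]² = 151.3, so 152 (153 by exact binomial).

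**4. Power of a six-month OS test at 93.** Complete follow-up to six months is assumed.

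| Method | Power |
|---|---|
| Exact binomial (reject if 39 or fewer alive; actual alpha 0.024) | 71.0% |
| Normal approximation, null variance | 71.7% |
| Normal approximation, alternative variance | 73.0% |
| Arcsine | 71.6% |
| Complementary log-log | 68.6% |
| Simulation | 71.4% |

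Under the alternative such a test uses about 93 × 0.603 = 56 of the 83 expected deaths. The chance of missing a true 4.5-month median would be about 29%, against the planned 10%.

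**5. The 4.5-month limit read literally.** If the rule is to reject when the estimated median is 4.5 months or less, a treatment whose true median is 4.5 months is rejected only about 50% of the time, because the estimate falls on either side of the true value about equally often. This is a third rule, and it has neither the 90% nor the 71%.

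**The case against.** The strongest reply is that this is loose wording. Median OS is used in the abstract, the objective, the hypotheses and the limit. The sentence in the analysis plan announces a calculation, not a test, and groups OS with two outcomes that really are six-month rates. Kaplan-Meier estimation would yield the median as well. Much of this stands, and it makes the repair easy. It does not remove the contradiction: the six-month label appears in two sections, and in the analysis plan it sits in the only sentence that ties a calculation to the decision.

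A reader might infer that the trial has 71% power for OS. The documents do not support that. No six-month OS test is specified, and the 52.7% and 39.7% are derived here, not stated. The figure shows what would follow if the sentence were carried out as such a test.

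A reader might also infer that the planned test has been identified. It has not. The log-hazard form gives 93 for OS but 75 and 58 for the control rates, against the stated 71 and 53. The cube-root form gives 71 and 53 but 90 for OS. What survives is that every variant is exponential and uses all events.

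The control rates were apparently sized the same way. A strict six-month proportion test would need about 158 and 122 patients, with about 73% and 83% power at 93. That is fair, and those tests should be named with the same care. But the control rates have hypotheses and limits stated on the six-month scale, so the contradiction of endpoint is confined to OS.

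Finally, the full protocol is an additional file that is not shown and may name the test. The point is not that detail is missing; the article itself states two different OS quantities.

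**Conclusion.** The point holds as an inconsistency in the decision rule for a primary outcome. The article defines, sizes and limits OS on the median, then decides on six-month OS without a null value, alternative or limit. The contradiction rests on the text alone.

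The size of the consequence is conditional. With exponential survival and complete follow-up to six months, a one-sided 0.025 test of six-month OS would have about 71% power at 93 patients (69-73%), against about 90-92% for an all-deaths test of the kind that reproduces the 93. A suspicion that the rule could be picked after seeing the data should not be pressed far, since the only OS hypotheses and limit in the article are for the median.

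**What to change.** - **Statistical analysis plan section:** name one OS decision test, a one-sample test against a 6.5-month median (exponential or one-sample log-rank), using all follow-up to 6 months after the last patient is accrued, one-sided 0.025, in a version that holds that level. Report six-month OS descriptively.
- **Sample-size section:** replace the reference to a six-month OS endpoint with median OS, and rest the statement on loss to follow-up on the censored survival analysis.
- **Sample-size section:** restate the OS limit of 4.5 months as the alternative value of that test, not as a cut-off for the point estimate, so that a single OS rule remains.

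The cost is a few sentences in two sections, with the same patients, data and timing. The other consistent course, keeping six-month OS as the decision quantity, would need stated null and alternative values and about 152 patients for 90% power under the assumptions above.
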